Stimulus–Response (S-R) paradigm, a modified version of the methodology proposed by Colzato et al. [53] and Rawish et al. [54], will be employed and adapted to better approximate real-life contexts. Whereas the original studies examined the neural processes involved in file event processing, our approach will incorporate scenarios with greater ecological validity.

Participants will be seated in front of a 15.6-inch (39.6 cm) computer screen, maintaining a viewing distance of approximately 60 cm. The stimulus–response paradigm will be implemented using OpenSesame software, version 4.0.29 (for Windows, OpenSesame Inc., Portland, OR, USA), developed by Sebastiaan Mathôt: https://osdoc.cogsci.nl/4.0/download/ (accessed on 3 September 2024), for the presentation of visual stimuli. The paradigm will follow the sequence described below (see Figure 2):Pre-Cue: A black screen with a white plus symbol (“+”, 64 × 64 pixels) will be displayed for 1500 milliseconds;Cue: A 1500-millisecond video will be shown featuring a woman walking either to the left or right across a pedestrian crossing. The walking direction will be randomized;Pre-S1: An image of a store logo will be presented for 1000 milliseconds;Stimulus S1: A second video (3000 milliseconds) will be shown, in which the same woman will continues walking on the pedestrian crossing and displays an unexpected behavior in response to a balance loss. To recover, she performs a compensatory stepping strategy: either a lateral step or a forward step. A visual distractor (a red or grey car) will also be present in the background;Pre-S2: The same store logo image will be shown again, now for 2000 milliseconds;Stimulus S2: A second instance of the stimulus will be presented, with the same characteristics as S1 but randomized.

The paradigm will include two conditions related to feature overlap between S1 and S2:Complete feature overlap (S1 = S2): Same stepping strategy and same car color;No feature overlap (S1 ≠ S2): Different strategy and different car color.

During each trial (S1 and S2), participants will provide two responses (R1 and R2) by pressing either the left or right control key with their index fingers.

R1: Participants will memorize the walking direction shown in the Cue phase (left or right) and respond with the corresponding key when S1 appears;R2: Participants will quickly indicate the stepping strategy shown in S2: the left key for a forward step and the right key for a lateral step.

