This task structure will allow for the identification of four conditions based on response and feature overlap:(a)Stimulus feature overlap with response repetition (S1 = S2 and R1 = R2);(b)Stimulus feature overlap with response alternation (S1 = S2 and R1 ≠ R2);(c)No stimulus feature overlap with response repetition (S1 ≠ S2 and R1 = R2);(d)No stimulus feature overlap with response alternation (S1 ≠ S2 and R1 ≠ R2).

The full task consists of 80 trials, distributed across five blocks of 40 trials each. Reaction times and response accuracy will be recorded throughout the experiment. Prior to the actual task, participants will complete a 5-min practice session without wearing the EEG recording cap.

During this test, EEG and HRV will be recorded. To achieve this, the Enobio^®^ instrument (Neuroelectrics, Cambridge, MA, USA) and the OpenSesame software, version 4.0.29 (for Windows, OpenSesame Inc., Portland, OR, USA)will be synchronized using the Lab Streaming Layer (LSL). EEG time–frequency analysis will be performed specifically within this paradigm to examine neural dynamics associated with the different task events. EEG data will be epoched relative to the onset of S2 (0 ms) and segmented according to task phases (Figure 3): Pre-Cue (−9000 to −7500 ms), Pre-S1 (−6000 to −5000 ms), S1 (−5000 to −2000 ms), Pre-S2 (−2000 to 0 ms), and the within-trial interval (0 to 1000 ms). Time–frequency decomposition will be conducted using Morlet wavelets (width = 5 cycles) with a Hanning taper. For each electrode and time point, the average spectral power will be computed within the theta (4–7 Hz), alpha (8–12 Hz), and beta (12–30 Hz) frequency bands. Comparisons will be performed between stepping strategies (lateral vs. forward) and task load (single-task vs. dual-task), with pointwise *t*-tests calculated for each time point in the 0–1000 ms window after S2 onset. False-Discovery Rate (FDR) correction will be applied to account for multiple comparisons, and effect sizes (r) will be reported for significant differences.

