**Figure 3 sports-14-00059-f003:**
[figure not shown]
Graphical representation of a single trial within the stimulus–response (S-R) paradigm adapted from Colzato et al. [53]. The temporal structure of the task is illustrated along a timeline. The pre-cue phase corresponds to the interval preceding cue presentation (from −9000 to −7500 ms relative to S2). The pre-S1 phase spans from to 6000 to 5000 ms, followed by the post-S1, which extends from 5000 to 2000 ms before the onset of S2. The pre-S2 interval covers the 2000 ms immediately preceding S2 (prone), whereas the post-S2 interval corresponding to the within-trial phase includes the 1000 ms following probe onset. Participants will be instructed to memorize the direction indicated by the cue. When stimulus S1 appears, they will respond by indicating the cue direction using the left or right control key. Upon presentation of S2, participants will identify the required movement, selecting the right control key for unloaded sidesteps and the left control key for a single forward step.

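### The lateral-versus-forward EEG contrast is tested only in the first 1000 ms of the S2 video, so part or all of the window may precede the step being compared

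*Protocol article*

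**What the plan says.** All of this stands in the protocol article, section 2.12.2 (Stimulus–Response Paradigm), and in the legend of Figure 3.

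- **S1.** "Stimulus S1: A second video (3000 milliseconds) will be shown". In it "the same woman will continues walking on the pedestrian crossing and displays an unexpected behavior in response to a balance loss". The step is the response to that event: "To recover, she performs a compensatory stepping strategy: either a lateral step or a forward step".
- **S2.** "A second instance of the stimulus will be presented, with the same characteristics as S1 but randomized". No separate duration is given for S2.
- **Response.** "R2: Participants will quickly indicate the stepping strategy shown in S2".
- **Epochs.** Time zero is S2 onset. S1 is segmented from −5000 to −2000 ms, which is its full length. The only segment after S2 onset runs from 0 to 1000 ms. The Figure 3 legend agrees: "the post-S2 interval corresponding to the within-trial phase includes the 1000 ms following probe onset".
- **Tests.** Lateral is compared with forward, and single-task with dual-task, by "pointwise *t*-tests calculated for each time point in the 0–1000 ms window after S2 onset", with false-discovery-rate correction.

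The article states neither when the step becomes visible in a clip nor why the S2 segment stops at 1000 ms.

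**The concern.** A short window locked to stimulus onset suits a static picture, whose content is complete at 0 ms. Here the stimulus is a film and the contrast is defined by an event inside it. Until the step begins, a lateral clip and a forward clip need not differ in the feature being compared. If the step comes late in the clip, the test may end before the difference between the conditions exists on screen.

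The Discussion anticipates theta, alpha and beta increases in this task and reads these rhythms through the event-file model. A null result from a window that may not contain the step could not be interpreted, even for generating hypotheses. A positive result early in the window would have an uncertain source.

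**Working it through.** **1. Reproduce the timeline.** Phase durations from the task description in section 2.12.2: Pre-Cue 1500, Cue 1500, Pre-S1 1000, S1 3000, Pre-S2 2000 ms.

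1500 + 1500 + 1000 + 3000 + 2000 = 9000 ms, which matches the stated start of the epoch at −9000 ms. Placed in order:

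| Phase | Start (ms) | End (ms) |
|---|---|---|
| Pre-Cue | −9000 | −7500 |
| Cue | −7500 | −6000 |
| Pre-S1 | −6000 | −5000 |
| S1 | −5000 | −2000 |
| Pre-S2 | −2000 | 0 |

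Every boundary that the article states is reproduced. So 0 ms is the first frame of the S2 clip, not the step.

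**2. Share of the clip tested.** Assumption: S2 lasts 3000 ms, inferred from its having the same characteristics as S1. Then 1000/3000 = 33% of the clip is tested and 2000 ms (67%) is not. The same kind of clip at S1 is segmented over all of its 3000 ms.

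**3. Tested time after the step.** The step onset *s* is not given, so it is varied as an assumption. Post-step time tested = max(0, 1000 − *s*). Share of the window before the step = min(1, *s*/1000).

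| Assumed step onset (ms) | Post-step time tested (ms) | Share of window before the step |
|---|---|---|
| 0 | 1000 | 0% |
| 250 | 750 | 25% |
| 500 | 500 | 50% |
| 750 | 250 | 75% |
| 1000 or later | 0 | 100% |

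The first row does not fit the described order of events, since walking and the loss of balance come before the step. For any onset after 0 ms, some of the window precedes the contrasted feature.

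**4. Effect on the multiplicity family.** Signals are sampled at 500 Hz. If power is tested at every sample (an assumption), the window holds 500 × 1 s = 500 tests per electrode and band. With a step onset at 500 ms, 250 of them precede the step; at 1000 ms or later, all 500 do.

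**5. What the early time points can show.** The article lists two overlap conditions: same step with same car colour, or different step with different car colour. Colour match therefore goes with step match. If the car is in view early, its colour together with memory of S1 tells the participant which step is coming. An early lateral-versus-forward difference could then be anticipation drawn from the distractor. Locking to clip onset cannot separate this from processing of the step itself.

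**The case against.** The strongest reply is that the harm depends on a latency that the documents do not give. The article states the order of events but no times within the clip. The walk has already begun in the Cue video, so the loss of balance could come early in S2. The 3000 ms length of S2 is itself an inference, the drawing in Figure 3 was not available to this check, and frame-level timing is something a condensed article may leave out. This stands as far as it goes: a reader might infer that the step falls after the window, and the documents do not show that. What is fixed in print, however, is the window and its anchor, and the described order puts the step after the anchor.

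The second reply is that event-file retrieval could start at S2 onset, because car colour and memory of S1 can predict the step. This also stands. It rules out the stronger reading that R2 can be chosen only once the step is visible. It does not rescue the window, because it adds a second explanation for any early effect.

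Two further inferences should not be drawn.

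- **Reaction times.** A reader might conclude that they are biased between step types. The article gives no starting point for reaction time and plans no such comparison. If the same clips are used in both arms and at both visits, a fixed delay per clip would largely cancel in the changes over time or between groups.
- **Whole analysis.** A reader might extend the point to everything done with this task. The single-task versus dual-task comparison does not depend on seeing the step.

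**Conclusion.** The concern holds in a limited form. The lateral-versus-forward contrast is tested in a window anchored to the start of the S2 video, although the feature that defines the contrast appears later in that video. For assumed step onsets from 250 ms to 1000 ms or later, between 25% and 100% of the window precedes the step. Those time points add tests that are uninformative about the step as seen, and early effects may reflect prediction.

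This rests on two assumptions: that S2 lasts 3000 ms like S1 (needed only for the one-third figure), and the range of step onsets. It is not shown that the step falls outside the window.

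The article classes these measures as secondary and exploratory. No primary outcome and no primary between-group conclusion changes. The point is still worth correcting, because the remedy is cheap and the contrast may otherwise be uninterpretable.

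**What to change.** 1. For each clip, record the frame at which the step becomes visible, and log clip identity on every trial.
2. Lock the S2 epochs for the lateral-versus-forward contrast to that frame. If this is not possible, extend the S2 window at least to the end of the clip.
3. Fix the choice before analysis, so that the window is not selected from the data. Keep the onset-locked 0–1000 ms window as descriptive.
4. If reaction times are ever compared between step types, measure them from the same frame.

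**Cost.** EEG is already recorded during the task and synchronised with the stimulus software. Because the step frame is constant within a clip, epochs can be re-locked offline, provided clip identity is logged and recording continues through S2. The clips need not be re-edited. Choosing the first visible frame calls for a judgement that should be written down.

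**Downside.** Later epochs contain more response-related artefact. Extending the window instead adds time points to the false-discovery-rate family: with a 3000 ms clip there would be 3000/1000 = 3 times as many.

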### 2.13. Data Analysis

The collected outcomes will be compiled in an anonymized database for statistical processing. Both descriptive statistics and inferential analyses will be conducted. Data analysis will be performed using the Statistical Package for the Social Sciences software (SPSS, version 25.0; IBM Corp., Armonk, NY, USA). The Shapiro–Wilk and Kolmogorov–Smirnov test will be used to assess the normality of all variables.

Furthermore, to explore the effect of physical exercise intervention, physical performance tests will be analyzed under both single task and dual-task conditions. Dual-task cost will be calculated to quantify the impact of performing a cognitive task on physical performance. Given the cluster-randomized design, changes over time and between-group differences were analyzed using linear mixed-effects models, accounting for the hierarchical structure of the data, with participants nested within fibromyalgia associations. Group (intervention vs. control), time, and their interaction (group × time) were included as fixed effects. Random intercepts were specified for associations and for participants, and random slopes were included when appropriate, assuming an unstructured covariance matrix. The normality of model residuals was visually assessed for all variables.

To quantify the degree of clustering, the intra-cluster correlation coefficient (ICC) will estimate from the variance components of the mixed-effects models, calculated as the ratio of between-association variance to total variance (between-association plus residual variance). This parameter will be used to evaluate the magnitude of within-association dependence and to confirm the appropriateness of the cluster-adjusted analytical approach.

In the event of participant attrition or missing data due to insufficient attendance, the analyses will follow an intention-to-treat approach, whereby all randomized participants will be included in the analysis according to their originally assigned group regardless of their level of adherence to the intervention. To address missing outcome data, an appropriate imputation strategy will be applied. Where necessary, missing outcome data will be handled using multiple imputations methods. This procedure will be performed following the assumptions for missing at random. When imputation is not feasible, the last observation carried forward or baseline-value carried forward strategies will be applied, depending on data characteristics. In addition, a per-protocol sensitivity analysis will be conducted including only participants who attend the majority of the scheduled sessions to evaluate the robustness of the findings and account for intervention dose–response effects.

The alpha level of significance (0.05) will be adjusted according to the Benjamini–Hochberg procedure to avoid type I error derived from multiple comparisons [55]. Effects sizes were computed and interpreted according to discipline-specific thresholds recommended for physiotherapy and rehabilitation research [56]. For measures of individual differences (Pearson’s r), effect sizes of 0.3, 0.5, and 0.6 were interpreted as small, medium, and large, respectively. For group differences (Cohen’s d or Hedges’ g), effect sizes of 0.1, 0.4, and 0.8 were considered small, medium, and large, respectively.

EEG measures were included as secondary, exploratory outcomes. Although an exploratory hypothesis regarding changes in beta power was formulated based on previous literature [57], EEG analyses were not designed as confirmatory and were conducted to generate mechanistic insights. To reduce the number of comparisons and improve statistical power, regions of interest (ROIs) were defined as a priori by grouping electrodes according to anatomical location: frontal (Fp1, Fp2, F3, F4, and Fz), central (C3, C4, and Cz), and parietal (P3, P4, and Pz). Mean spectral power was computed for each frequency band within each ROI by averaging across electrodes. For exploratory analyses, a 2 × 2 factorial design implemented within the EEGLAB STUDY framework was used to examine EEG data before and after the intervention in alpha and theta bands. Permutation-based statistical testing with 2000 iterations was applied, and multiple comparisons were controlled using the false-discovery rate (FDR) correction.

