## 2. Materials and Methods

### 2.1. Study Design

This study will be a randomized controlled trial with a parallel group design (pretest–post-test control group design) [19]. Participants will be recruited from FM associations in the region of Extremadura (Cáceres, Almendralejo, Hervás and Olivenza) in Spain. Each FM association will be randomly assigned to either the intervention group, which will participate in a structured physical activity program or to the control group. To ensure methodological rigor and high-quality reporting consistency with clinical trial standards, the study will follow the SPIRIT 2013 Statement guidelines and will apply the TESTEX 2015 scale, a tool specifically developed to evaluate the quality and reporting standards of exercise training studies [20].

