#### 2.2.2. Recruitment

The sample size will be calculated based on one of the study’s primary outcomes, i.e., the impact of FM. Data from a previous study [22] that will be used as a reference evaluated the effects of a creative dance intervention on this outcome. In that study, the impact of FM was reduced by 1.16 points compared with the control group after six weeks of intervention.

According to the results obtained in the G*Power statistical power analysis software version 3.1.9.7 (Heinrich Heine University Düsseldorf, Düsseldorf, Germany), assuming an effect size of f(V) = 0.98, a power of 85%, and a significance level of 0.05, a sample size of 22 people per intervention group is estimated. However, considering an anticipated dropout rate of 10%, a total of 44 participants (22 per group) will be needed to observe a significant effect.

Therefore, the participants recruitment will take place between January and March 2026. Both groups will consist of women with FM (exercise group: *n* = 22; and control group: *n* = 22) recruited from different FM associations in the region of Extremadura.

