### 2.3. Randomization of Assessments

The assessments will follow a fixed sequence with alternating tests of the upper and lower limbs, thereby ensuring adequate rest periods to prevent cumulative fatigue and optimizing the overall time required for the evaluations. To reduce familiarization and learning effects, the sequence of specific conditions will be randomized. Randomization will apply to both the physical test conditions and the arithmetic cognitive task.

The physical tasks that each participant will complete at baseline (pre) and post-intervention will be scheduled across two assessment days:Day 1: Cognitive task (arithmetic-based counting test), handgrip strength, timed up and go test (TUG), arm curl test (ACT), and 30 s chair stand test (CST). Randomization: The random allocation sequence will be generated by an independent researcher using a computer-based random number generator (Random Number Generator tool; Google, LLC., Mountain View, CA, USA) and implemented via a password-protected Excel file. Simple randomization (0/1) will be used for Day 1 tasks. Personnel responsible for enrolling participants and conducting assessments will remain blinded to the random allocation sequence. Two aspects will be randomized for each participant: (1) whether the arithmetic subtraction task is performed at the beginning (coded as 1) or at the end (coded as 0) of the physical test sequence and (2) whether the motor task is performed as a single-task condition (coded as 0) or as a dual-task combined with the cognitive subtraction task (coded as 1). The handgrip test will be performed without dual-task condition due to its temporal execution characteristics;Day 2: Baseline resting Electroencephalography (EEG) and Heart Rate Variability (HRV), EEG and HRV combined with the Stimulus–Response (S-R) paradigm protocol, Short Physical Performance Battery (SPPB), and Agility Challenge for the Elderly (ACE). Randomization: Only the spatial orientation component of the ACE test will be randomized according to the recommendations of Lichtenstein et al. [23]. The random allocation sequence for this task will also be generated by the independent researcher, recorded in the same password-protected Excel file, and accessed by the researcher immediately prior to testing to ensure allocation concealment

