### 2.4. Clusters Randomization

The clusters in this study are FM associations from the region of Extremadura (Cáceres, Almendralejo, Hervás, and Olivenza) in Spain. Each association will be randomly assigned to either the intervention group, which will participate in a structured physical activity program, or to the control group. The allocation sequence for the associations will be created using a computer-generated random number system (Random Number Generator tool; Google, LLC., Mountain View, CA, USA). Simple randomization will be applied, with no stratification, given the small number of clusters. The sequence will be recorded in a password-protected Excel file. Personnel responsible for enrolling associations and implementing the intervention will remain blinded to the allocation sequence until each cluster is assigned. The principal investigator (IP) will provide the group assignment immediately prior to the start of the intervention for each association, ensuring allocation concealment.

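### The between-group estimate in Section 2.13 is in effect a difference in mean change. Adjusting for each woman's baseline value would usually be more precise, at no data cost.

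*Protocol article*

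**What the plan says.** Section 2.1 describes a "randomized controlled trial with a parallel group design (pretest–post-test control group design". Section 2.3 gives the measurement times: "The physical tasks that each participant will complete at baseline (pre) and post-intervention will be scheduled across two assessment days". Section 2.7 likewise has one pre-intervention and one post-intervention assessment.

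Section 2.13 sets the model. On fixed effects: "Group (intervention vs. control), time, and their interaction (group × time) were included as fixed effects". On random effects: "Random intercepts were specified for associations and for participants, and random slopes were included when appropriate, assuming an unstructured covariance matrix". No section enters the baseline value as a covariate or constrains the arms to a common baseline mean. Baseline therefore appears only as the first outcome row, with a free difference between the arms.

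Section 2.4 names the randomised units: "The clusters in this study are FM associations from the region of Extremadura (Cáceres, Almendralejo, Hervás, and Olivenza) in Spain". On the method of allocation it says: "Simple randomization will be applied, with no stratification, given the small number of clusters".

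**The concern.** With one value before and one after, a group × time coefficient fixes the slope on the pre-test at 1. The estimated slope is normally below 1, and using it removes variance that the change score retains. The baseline values are already collected and the trial has only 44 women, so the precision is available for one sentence of analysis text.

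A second consideration is chance imbalance. When arms differ at baseline through participant-level variation, part of that gap regresses by the second visit and enters the change-score estimate with reversed sign. An exercise arm that happened to start worse would look somewhat better than it should. Simple randomisation of four associations does nothing to limit baseline gaps.

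At stake is the width of the confidence intervals for the primary outcomes. The validity of the test is not at stake.

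**Working it through.** **Inputs.** From the article: 22 women per group, effect size 0.98, 85% power, α = 0.05, 10% dropout (Section 2.2.2); four associations (Section 2.4); the fixed and random effects (Section 2.13). Assumed, because the article does not give them: two-sided testing, ρ, the ICC, the correlation c between an association's pre and post effects, and a split of two associations of 11 women per arm. Simple randomisation does not guarantee that split.

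**The plan's own figure.** The article states "a power of 85%, and a significance level of 0.05, a sample size of 22 people per intervention group is estimated". Reading 0.98 as a standardised mean difference, a two-sample t-test needs 20 per group (power 85.5%) and the normal approximation needs 19. Allowing for 10% dropout, 19/0.9 rounds up to 22 and 20/0.9 to 23, so 22 is reproduced. None of these calculations includes clustering.

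**The interaction is a change-score contrast.** In three simulated complete datasets with four equal associations and random intercepts for association and participant, the fitted group × time coefficient equalled the raw difference in mean change (for example 0.37964 for both).

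**Precision without clustering.** With σ² the variance at each visit:
- change score: 2(1−ρ)σ²
- post value adjusted for baseline: (1−ρ²)σ²
- ratio adjusted/change: (1−ρ²)/[2(1−ρ)] = (1+ρ)/2

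| ρ | 0.3 | 0.5 | 0.7 | 0.8 | 0.9 |
|---|---|---|---|---|---|
| ratio | 0.65 | 0.75 | 0.85 | 0.90 | 0.95 |

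If the change-score contrast had exactly 85% power at 22 per group (a difference of 0.925 change-score SDs), adjustment would give 93.3% at ρ = 0.5 and 90.1% at ρ = 0.7. These figures ignore the associations.

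**Precision with two associations of 11 per arm.** Per arm, with total variance 1 and I for the ICC:
- change: I(1−c) + (1−I)·2(1−ρ)/22
- adjusted: I(1+ρ²−2ρc)/2 + (1−I)(1−ρ²)/22

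At ρ = 0.5, I = 0.05:
- c = 0.8: change 0.0100 + 0.0432 = 0.0532; adjusted 0.0113 + 0.0324 = 0.0436; ratio 0.82
- c = 1: change 0.0432; adjusted 0.0063 + 0.0324 = 0.0386; ratio 0.89

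| ICC (ρ = 0.5) | 0.01 | 0.05 | 0.10 | 0.20 |
|---|---|---|---|---|
| ratio, c = 0.8 | 0.77 | 0.82 | 0.87 | 0.95 |
| ratio, c = 1 | 0.78 | 0.89 | 1.06 | 1.44 |

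With c = 1, setting the two variances equal gives I/2 = (1−I)/22, so I = 1/12 = 0.083 whatever ρ is.

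**Power with four associations.** Taking 2 degrees of freedom, the same effect and ρ = 0.5, power (change → adjusted) is about 36% → 41% (ICC 0.05, c = 0.8), 41% → 45% (ICC 0.05, c = 1) and 43% → 41% (ICC 0.10, c = 1).

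**Baseline gaps.** Let w be the participant-level share of the variance of the arm gap at baseline: w = [(1−I)/22] / [I/2 + (1−I)/22]. With c = 1 and an adjustment slope of ρ, the part of a baseline gap carried into the estimate is −(1−ρ)w for the change score and +(1−ρ)(1−w) for the adjusted estimate. At ρ = 0.5:
- ICC 0: w = 1; −0.50 and 0
- ICC 0.05: w = 0.63; −0.32 and +0.18
- ICC 0.10: w = 0.45; −0.23 and +0.28

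Simulation of a participant-level regression gave similar values: −0.50 and 0.00, −0.31 and +0.18, −0.22 and +0.25. Both estimators averaged about zero over randomisations when there was no treatment effect.

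**The case against.** The strongest objection is that this is individually randomised reasoning applied to a trial that randomises four associations. A stable difference between associations cancels in a change score, whereas adjustment with a slope near ρ leaves about (1−ρ) of it in the estimate. With few unstratified clusters, association-level gaps are the kind to expect. This stands: the precision gain shrinks with clustering and can reverse, and the regression-to-the-mean argument holds fully only for participant-level gaps.

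A reader might infer that the planned estimate is biased by regression to the mean. The documents do not support that. Neither estimator is biased over randomisations, and once the ICC exceeds about 0.083 with stable association effects, the adjusted estimate carries more of a baseline gap than the change score does.

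A reader might also infer that the plan gives up 25% of variance or about 8 points of power. Those are the no-clustering values at an assumed ρ of 0.5.

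Two further objections hold in part. H1 asks about improvement against both baseline status and the control group, and the group × time model speaks to both; that is a reason to retain it, but does not require it to supply the primary between-group estimate. The equality with the change-score contrast is exact only for complete data and equal associations. Random slopes or imputation alter it slightly without adding baseline adjustment.

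**Conclusion.** The point holds as a cheap improvement. The planned model is standard and its test is valid, but its between-group estimate does not use the baseline value as a covariate and is usually less precise than it could be. The individual-level variance ratio is 0.75 at ρ = 0.5 and 0.85 at ρ = 0.7. With two associations of 11 per arm, ρ = 0.5 and an ICC of 0.05, it is about 0.82 to 0.89. Adjustment brings no gain at an ICC of about 0.083 with fully stable association effects, and loses precision above that. With less stable effects (c = 0.8), a gain remains at every ICC tabulated, up to 0.20.

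The conclusion rests on assumed values of ρ, the ICC and the stability of association effects, and on an even split of associations and women. Baseline adjustment does not cure the limits of a four-cluster design.

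**What to change.** In Section 2.13, make the primary between-group estimate for each primary outcome the post-intervention value, modelled on group and the participant's own baseline value of the same outcome and the same task condition (single or dual), keeping the association term. Report the group coefficient with its 95% CI. Keep the group × time model as a prespecified sensitivity analysis and for the within-group change that H1 asks about.

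The cost is a sentence or two of wording and one extra coefficient, with no new data, visits or participants. Women without a baseline value would need the multiple imputation already planned in the same section. If associations differ strongly and stably (ICC above about 0.08), there is no gain or a loss of precision, which the retained group × time analysis would show. Fixing the choice now also avoids selecting between adjusted and unadjusted results after baseline differences have been seen.
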